## Background

Overweight and obesity affect almost two-thirds of New Zealand adults and rates continue to climb in some ethnic and demographic groups [1]. The inability of many individuals to lose significant weight by themselves or for most to keep it off is due to a myriad of factors including making changes to lifestyle that are too drastic and therefore not sustainable, the widespread availability of energy-dense foods and sedentary past-times, changes to work and leisure-time energy expenditure, and insufficient support structures [2, 3]. However, considerable debate and confusion also exists in both lay and scientific literature regarding whether there is an “optimal” dietary composition for weight loss [4]. Low-carbohydrate diets in particular have long been purported to have metabolic and clinical advantages over other dietary patterns [5–7]. It makes mechanistic sense that lower carbohydrate diets *could* promote greater weight loss, principally because of a reduction in insulin levels reducing the storage of body fat [8]. However, at the practical level, recent meta-analyses suggest little difference in weight and health outcomes between diets differing quite markedly in macronutrient composition, particularly over time frames longer than 6 months [9–13]. Instead, a far more relevant factor appears to be the degree of *adherence* to the prescribed diet [11, 14, 15], an aspect that is insufficiently measured [16].

Such findings have led expert groups to recommend that the most suitable diets are not those that include a specific nutrient composition per se, but rather ones that entail moderate energy restriction which participants are willing and able to follow long-term [17]. It is becoming clear that several acceptable dietary patterns that differ quite markedly in terms of macronutrient composition are suitable for weight loss. The more important question then becomes how best to encourage and support long-term compliance with one, or more, of these patterns [18]. However, while adherence to dietary change is viewed as a cornerstone of non-communicable disease prevention and management [19], little practical guidance is available identifying which specific factors enhance adherence to dietary advice [3]. The short-term nature of most studies, marked differences in terms of how adherence is assessed, and overall low trial quality limits firm conclusions being drawn about the most efficacious factors [3].

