Two promising and popular dietary approaches, despite relatively little research around their use in humans, include paleolithic diets and intermittent fasting. Paleolithic diets are based on evolutionary principles and include meat, fruit, vegetables and nuts/seeds while eschewing grains, dairy, and processed foods. Early small studies have provided encouraging results [54–56]. However, whether overweight adults can adhere to paleolithic-type diets in the longer-term requires study. Intermittent fasting is usually defined as normal food intake 3–5 days a week and dramatically reduced intake (down to 2 MJ from typical intake of 8–10 MJ) for 2–4 days. Anecdotally this is believed to be much easier than reducing energy intake by a smaller amount (usually 2 MJ/day) *every* day, which forms part of the current guidelines. While a wealth of animal data supports the effectiveness of intermittent fasting for weight control [57], research in humans is less certain [58]. However, the small amount of data available does show modest evidence of effectiveness for treatment of obesity and cardioprotection [59, 60].

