Exercise produces more successful weight loss than dietary change alone [61, 62], seems particularly important for weight maintenance [63] and has many additional health benefits, over and above that relating to energy balance. Regular physical exercise is associated with an approximate halving in the risk of cardiovascular disease [64], can decrease the incidence of diabetes by up to 50 % as part of lifestyle counselling [65], and even decrease insulin resistance in those with established metabolic syndrome [66]. However, a major public health challenge is how best to encourage people to be physically active on a regular basis. Although evidence that regular physical exercise is beneficial is overwhelming [67], adherence remains a major issue [68], with lack of time often cited as a major barrier [69]. Thus there has been increasing interest in ascertaining the minimum amount of exercise required that might produce effective health benefits. An alternative to meeting moderate to vigorous physical activity (MVPA) guidelines may be the promotion of high intensity interval training (HIIT). In HIIT, brief periods of high-intensity exercise are interposed with recovery periods at a much lower intensity [70]. Although HIIT regimes typically include 10 minutes or so of intense exercise performed three times per week, as little as 3 minutes of intense exercise per week has been shown to produce cardiovascular and metabolic improvements [71, 72], although effects on body composition are less certain [73]. Although HIIT holds promise, virtually all research to date has been conducted in the laboratory and it is uncertain whether these findings will translate into community settings. If people cannot complete HIIT by themselves, its efficacy as a public health approach is very limited. Whether participants can adhere to a HIIT training regime long-term is also not currently known.

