### Statistical analyses and power calculations

Based on a standard deviation (SD) for baseline weight of 15 kg, and a correlation between repeat measures of r = 0.90 (obtained from our previous studies involving similar populations), our study has 90 % power using a two-sided 5 % level of significance to detect a clinically important difference in change in body weight of 4 kg between any pair of groups with 42 participants per group. While this may be viewed as a large difference, anything smaller does not really represent a difference of any importance between strategies. Thus we will recruit 250 participants in total across the five groups which allows for 15 % drop-out/unusable data. Fifty per group at baseline also provides 80 % power to detect differences of 5 cm in waist circumference (baseline SD 12, r = 0.80).

The primary analysis will follow modified intention-to-treat principles (using all available data) and will compare the outcomes resulting from the five different support strategies (*RCT analysis*). Linear mixed models will be used to model outcomes at 6, 12 and 24 months after adjusting for baseline values. Standard mixed model diagnostics will be performed. Although this analysis does not take diet and exercise choice into account because meta-analyses show there is little difference in outcomes from different treatments, further analysis adjusting for diet and exercise will be considered.

However, because participants do have choice over which diet and exercise plan they would like to follow, we are able to investigate the data in a number of ways. The baseline data will allow a *cross-sectional analysis* to assess the popularity of approaches among participants and then to examine what it is about people that lead them to choose to follow these different diet and exercise approaches (subject to sufficient numbers choosing each approach). Once the RCT analysis has been completed, we will be able to undertake a *cohort analysis* to determine whether adherence differs for each of the different diet and exercise approaches, subject to sufficient numbers making that particular choice, and how this differing adherence affects our study outcomes of interest.

All analyses will be performed using Stata 13.1 or a later version with all statistical tests performed at the two-sided 0.05 level.

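### The reason given for leaving diet and exercise choice out of the primary model does not support that decision, and adjusting for the pre-randomisation choice is cheap and may add some precision

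*Protocol article*

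**What the plan says.** All references are to the Protocol article.

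- **Statistical analyses and power calculations.** The primary analysis compares the five support strategies with linear mixed models for 6, 12 and 24 months, adjusted for baseline values and using all available data. It states that "this analysis does not take diet and exercise choice into account because meta-analyses show there is little difference in outcomes from different treatments". The same sentence says that an adjusted analysis will be considered, without committing to it. Later, the baseline data are to be used to "examine what it is about people that lead them to choose to follow these different diet and exercise approaches".
- **Background.** On diets: "recent meta-analyses suggest little difference in weight and health outcomes between diets differing quite markedly in macronutrient composition", particularly beyond 6 months. On intermittent fasting, after the animal data: "research in humans is less certain". Paleolithic diets are supported by small early studies. On HIIT: "although effects on body composition are less certain", with nearly all research done in the laboratory.
- **Aims and objectives.** The diet evidence is described as an absence of evidence of important differences. Adherence to, and outcomes within, the self-selected plan groups form secondary aim (iii).
- **Choice of diet and exercise plan; Randomisation.** Participants choose first and are randomised afterwards, stratified by sex only.
- **Intervention groups and sessions.** Those already randomised to control meet staff to discuss which diet and exercise options would suit them.

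**The concern.** The article makes an explicit modelling decision and gives a reason for it, so the reason can be tested. It has three weaknesses.

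1. **Coverage.** The evidence described concerns the macronutrient composition of diets. The decision also covers exercise choice, for which no meta-analysis is described, and two diets on which the article itself calls human evidence limited.
2. **Relevance.** A small mean difference between diets is not the test for a useful baseline covariate. Plans here are self-selected, and a comparison of diets cannot show that the people who pick them have the same prognosis.
3. **Other outcomes.** The same model serves dietary intake, accelerometry and aerobic fitness. The plans are meant to change several of these directly, so little difference is least credible there.

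What is at stake is some precision in the strategy contrasts, and some protection against bias if dropout depends jointly on plan and arm. A likelihood-based mixed model handles only missingness explained by the variables in it.

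**Working it through.** **The plan's own figure.** The article claims "90 % power using a two-sided 5 % level of significance" for a "difference in change in body weight of 4 kg between any pair of groups with 42 participants per group", from a "standard deviation (SD) for baseline weight of 15 kg" and a correlation of 0.90. With baseline adjustment and two averaged follow-ups (equal correlations), the residual SD is 15 × √((1 + 0.90)/2 − 0.90²) = 15 × √0.14 = 5.61 kg. This gives 42 per group, with power 90.4 %. Then 42/0.85 = 49.4, rounded up to 50 per group, or 250 in all. The figure reproduces on that reading. With one follow-up the residual SD is 15 × √(1 − 0.81) = 6.54 kg, and 42 per group gives 80.0 % power.

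**Assumptions from here on.** The article gives no plan mix, plan effect or dropout by plan. I assume that a plan is chosen by a share p of 0.2 to 0.5, and that it differs by D = 2 to 4 kg in weight.

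**Precision for weight.** The share of residual variance explained by plan is R² = p(1−p)D² / (6.54² + p(1−p)D²), and the standard error is multiplied by √(1 − R²).

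- p = 0.2, D = 2: R² = 0.64/(42.75 + 0.64) = 1.5 %, so the SE falls 0.7 %.
- p = 0.5, D = 4: R² = 4/(42.75 + 4) = 8.6 %, so the SE falls 4.4 %.

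The SE of a pairwise contrast, 6.54 × √(2/42) = 1.43 kg, becomes 1.42 to 1.36 kg. On the smaller residual SD of 5.61 kg the same formula gives falls of 1.0 to 5.8 %. In terms of power at 42 per group (from 90.4 %):

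| Residual variance explained by plan | Power | n per group for 90 % |
|---|---|---|
| 1 % | 90.7 % | 41 |
| 2 % | 91.0 % | 41 |
| 5 % | 91.8 % | 40 |
| 10 % | 93.1 % | 38 |

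**Precision for outcomes that the plans target.** If a plan shifts the outcome by one residual SD (assumed), R² = p(1−p)/(1 + p(1−p)).

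- p = 0.2: 0.16/1.16 = 13.8 %, so the SE falls 7 %.
- p = 0.5: 0.25/1.25 = 20 %, so the SE falls 11 %.

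Since 1/(1 − R²) is 1.16 to 1.25, this is like having 16 to 25 % more participants.

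**Dropout bias for weight.** Bias = D × (difference between arms in the plan share among completers).

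- Same dropout by plan in both arms: 0 kg, whatever D is.
- 50:50 split, one arm losing 5 % and 25 % by plan, the other 15 % in each: shares 0.95/(0.95 + 0.75) = 0.559 and 0.500. The difference of 0.059 gives 0.12 kg (D = 2) to 0.24 kg (D = 4).
- The 5 %/25 % pattern reversed between arms: the difference of 0.118 gives 0.24 to 0.47 kg.
- A harsher case: 40 % choose the plan, and its choosers drop out at 40 to 50 % in one arm. Everyone else drops out at 10 to 15 %.
  - Low end: 0.24/(0.24 + 0.51) = 0.32 against 0.40, times 2 kg = 0.16 kg.
  - High end: 0.20/(0.20 + 0.54) = 0.27 against 0.40, times 4 kg = 0.52 kg.

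If dropout occurs only after month 6, the 6-month weights absorb part of this. Given baseline, the correlation between two follow-ups is (0.90 − 0.81)/(1 − 0.81) = 0.474. About 1 − 0.474 = 0.526 of the bias then remains, so 0.16 to 0.52 kg becomes about 0.08 to 0.27 kg. Dropout before month 6 gets no such relief.

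**The case against.** The strongest reply is that nothing is wrong with the randomised comparison. Support strategy is allocated after the plan is chosen, so the contrasts are unbiased with complete data. Adjustment is optional, and a primary model without plan, followed by an adjusted one, is a defensible design. All of that stands. A reader might infer that the omission invalidates the primary comparison, and the documents do not support that.

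Other stronger readings also fail:

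- **That the cited evidence does not bear on the trial's outcomes.** The Background explicitly covers weight and health outcomes, especially beyond 6 months, and the primary outcome is weight at 12 and 24 months. The gap lies in exercise, in the specific plans, and in dietary intake, activity and fitness.
- **That the article expects choosers to differ in prognosis.** It only proposes to investigate what leads people to choose.
- **That a later adjusted model could displace the primary result.** The article fixes the model without plan as primary. What remains open is whether and how the adjusted one is run.
- **That precision is certainly lost.** If plans and their choosers do not differ, nothing is lost.

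The size objection is fair too. A 4 kg plan difference equals the trial's target effect. The harsher dropout case implies losing about 25 % of one arm (0.4 × 40 % + 0.6 × 15 %), against the 15 % planned. The article regards differences under 4 kg between strategies as unimportant. These points limit the gain for weight. They do not rescue the stated reason, and they say little about diet, activity and fitness.

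**Conclusion.** The point holds in a limited form. The stated reason does not justify leaving out diet and exercise choice: it concerns the macronutrient composition of diets, is silent on HIIT against guideline activity, and cannot speak to self-selection. The article's own secondary aim treats outcomes by plan as an open question.

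The consequence is a possible loss of efficiency and robustness, not a biased randomised comparison. For weight it is small: standard errors about 1 to 4 % lower with adjustment, and a dropout bias avoided of 0 to about 0.5 kg, arising only if plan predicts outcome and dropout by plan differs between arms. For dietary intake, activity and fitness it may be larger, about 7 to 11 % on the standard error. All these sizes rest on assumed plan shares, plan effects and dropout rates.

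**What to change.** In Statistical analyses and power calculations:

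1. Delete the little-difference reason.
2. Prespecify diet choice (3 levels) and exercise choice (2 levels), as recorded before randomisation, as fixed covariates in the mixed models for weight and the other outcomes.
3. Keep the model without them as a prespecified sensitivity analysis.
4. Reconcile Intervention groups and sessions, where controls discuss options after randomisation, with Choice of diet and exercise plan and with Randomisation, which put the choice first. The covariate must be the choice made before allocation in every arm.

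The cost is a sentence or two in the analysis section, no new data, and 2 + 1 = 3 degrees of freedom out of about 205 (5 × 42 = 210 completers less 5 group means). A category chosen by very few people may have to be merged, and the rule for that should be stated in advance.

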## Discussion

Despite continued debate regarding which diet is best for weight loss, it is becoming increasingly apparent that a variety of possible diets, ranging in macronutrient content, are suitable healthy options [17]. A more pressing issue thus becomes determining how best to support people to follow one of these approaches [89]. Determining whether high-intensity exercise can be a viable public health approach to improving weight and health is also warranted, particularly given an intriguing recent finding that MVPA is more consistently associated with body weight than is diet quality [90]. The SWIFT trial aims to compare five (including a control group) different ways of helping people to follow one of several possible dietary and exercise combinations, a choice that we believe should enhance adherence and thus success with weight management. We believe our trial offers a pragmatic way of assessing whether simple support strategies, that require limited to no expert involvement, are viable ways for overweight adults to successfully manage their weight over a two-year period.
